### Indications for early withdrawal

Participants may withdraw or be withdrawn from the study prematurely under specific circumstances to ensure their safety and the integrity of the research. The following criteria will guide decisions regarding early withdrawal:a)Significant Adverse Event (SAE): If a participant experiences a SAE that is deemed related to the intervention, they will be promptly withdrawn from the study. SAEs may include, but are not limited to, severe cardiovascular issues, psychiatric disturbances, or any other health complications that arise during the treatment period. The safety of participants is paramount, and frequent monitoring will be conducted to identify and address any adverse effects promptly. Recognised medication side effects, such as dry mouth, insomnia or mood changes will be discussed with the participant and managed according to participant toleration. Management may include a dose reduction.b)Withdrawal of Consent: If a participant chooses to withdraw, their decision will be respected. The participant will be invited to give the reason for withdrawal.

Through these early withdrawal criteria, we aim to uphold participant safety and maintain the quality and reliability of the study data. Any participant withdrawn from the study will be offered appropriate follow-up care and support as needed.

### Optimising attendance and handling missing data

To minimise missed follow-up assessments, all participants will be contacted ahead of their scheduled visits to confirm their attendance. If necessary, assessments can be postponed or rescheduled, with appropriate documentation maintained. Attendance at assessments during the dose titration phase is mandatory before considering any dose increases. Additionally, we will strive to collect follow-up data from participants who are unable to attend appointments during the maintenance dose phase or after treatment cessation by telephone. Participants will be asked to provide measurements taken from personal weight and blood pressure measuring equipment.

While we are committed to optimising adherence, some missing data are anticipated. To address this, we will compare baseline characteristics between participants with and without assessments at 6 and 24 months to identify potential biases in our final analysis. We will also investigate the reasons for study dropouts to better understand the mechanisms behind missing data, including any adherence issues related to the study protocol. Data will be reviewed regularly to identify missing or inconsistent entries, and where possible, clarification will be sought from the treating clinician or study records.

For the primary analysis, available data will be analysed using appropriate statistical methods depending on the extent and pattern of missingness. If the proportion of missing data is low, analyses will be conducted using complete case analysis. If missing data are substantial, appropriate statistical techniques such as multiple imputation will be considered to reduce potential bias.

Sensitivity analyses may be conducted to assess the impact of missing data on the primary outcome.

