### Outcome measures

Outcome measures will be collected at baseline, during each dose adjustment visit, during the maintenance phase of treatment, and following cessation of medication at 1 week, and at 1, 3, 6, 12, 18, and 24 months, as illustrated in Fig. 1.

Primary Outcome• Change in Body Weight: Change in body weight from baseline measured at 6 months during treatment and at 2 years following discontinuation of study medication.

Secondary Outcomes1.Cardiovascular Outcomes: Changes in cardiovascular parameters and the incidence of adverse cardiovascular events.2.Baseline Mental Health Assessment: Identification of possible undiagnosed active depressive disorders at baseline.3.Neuropsychiatric Effects: Changes in mood, cognition, and physiological responses during treatment as measured by the Amphetamine Interview Rating Scale (AIRS).4.Feasibility will be assessed by recruitment and retention rates, treatment adherence, ability to achieve target dosing, and the frequency of adverse events or treatment discontinuation.

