### Data collection

Data will be collected prospectively at predefined study time points. Assessments will occur at baseline, during each dose adjustment visit, throughout the maintenance phase, and following cessation of medication at 1 week and at 1, 3, 6, 12, 18, and 24 months, as outlined in Fig. 1.

At baseline, demographic data, medical history, current medications, and relevant clinical characteristics will be recorded. Baseline clinical assessments will include body weight, cardiovascular parameters (including ECG, echocardiogram, blood pressure and heart rate), and screening for possible undiagnosed depressive disorders.

During treatment and follow-up visits, body weight and cardiovascular parameters will be measured and recorded. Any adverse events, including cardiovascular events, will be documented throughout the study period. While participants are receiving the study medication, mood, cognition, and physiological responses will be assessed using the Amphetamine Interview Rating Scale (AIRS).

All data will be collected during routine general practice consultations by the treating clinician or trained study personnel and recorded in a secure electronic study database. Data completeness and accuracy will be monitored regularly, and any discrepancies will be reviewed and resolved where possible.

Participant information will be de-identified prior to analysis and stored securely in accordance with institutional data governance and privacy regulations.

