### Data analysis

The primary analysis will adopt an intention-to-treat approach to ensure that all randomised participants are included in the evaluation, regardless of adherence to the treatment protocol. The primary outcome, the change in weight from baseline to both 6 months and 2 years, will be assessed using simple and multiple linear regression, adjusting for prespecified covariates such as age, sex, baseline BMI, and comorbidities. Secondary outcomes, including cardiovascular parameters, mood and cognition (AIRS scores), and feasibility metrics, will be analysed using appropriate regression models or repeated-measures mixed-effects models for longitudinal data. Missing data will be addressed primarily using available data under intention to treat; where missingness exceeds 10–15%, multiple imputation and complete-case analyses will be conducted as sensitivity analyses. Exploratory subgroup analyses by sex, baseline BMI, or baseline depressive status may also be performed. Adverse events will be summarised descriptively by type, severity, and relationship to treatment, with serious events reported individually.

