### Reproducibility of study procedures

A comprehensive procedure manual has been created to standardise all aspects of the study, including patient recruitment, measurement assessment, data entry, management, analysis, and security. All study staff will receive training tailored to their specific roles. The manual includes detailed monitoring plans designed to safeguard patient welfare and ensure data integrity.

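### Weights from participants' own scales can enter the primary weight change unmarked and unpaired with the clinic baseline; the likely effect is small, but no planned analysis would show it

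*Protocol article*

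**What the plan says.** The section on optimising attendance and handling missing data provides telephone follow-up for "participants who are unable to attend appointments during the maintenance dose phase or after treatment cessation by telephone", and adds: "Participants will be asked to provide measurements taken from personal weight and blood pressure measuring equipment".

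Weight is the primary variable. The outcome measures section defines it as "Change in body weight from baseline measured at 6 months during treatment and at 2 years following discontinuation of study medication", and the data analysis section models "The primary outcome, the change in weight from baseline to both 6 months and 2 years" by linear regression, with no term for how the weight was obtained.

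On which data are used, the attendance section says: "For the primary analysis, available data will be analysed using appropriate statistical methods depending on the extent and pattern of missingness". On robustness it says: "Sensitivity analyses may be conducted to assess the impact of missing data on the primary outcome". The data analysis section adds multiple imputation and complete-case analyses once missingness passes 10–15%.

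Two other statements bear on this. The data collection section says: "All data will be collected during routine general practice consultations by the treating clinician or trained study personnel", which places the baseline weight in clinic and leaves no room for the telephone route. The reproducibility section says: "A comprehensive procedure manual has been created to standardise all aspects of the study, including patient recruitment, measurement assessment". That manual is not shown, and the article does not say that it covers home equipment.

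**The concern.** A change score assumes that both readings come from comparable instruments. Here the baseline is a clinic weight, and the follow-up may be a number read from an unchecked domestic scale and reported by telephone. The difference then contains true change, the offset between the two scales, and any self-report error.

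If home weights are equally common in both arms and carry the same offset, the offset cancels from the treatment contrast. If one arm misses more visits, it does not cancel. Where home reports read low, the arm with more of them appears to lose more weight. Unequal attendance is plausible for a drug whose dose is adjusted for tolerability, but the protocol neither predicts nor excludes it.

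The stated safeguards look elsewhere. A home weight counts as observed, so analyses aimed at missing data leave it untouched. It also reduces the apparent missingness, so the more the fallback is used, the less likely imputation is to be triggered.

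**Working it through.** The protocol gives no figure for scale offset, reporting error or share of home weights. Everything below that uses them is an assumption, shown over a range.

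**Inputs from the protocol**
- 29 per arm, design difference 6.5 kg, projected attrition 30% at 6 months (sample size section).
- SD of weight change 8.4 kg in the earlier single-arm study of 14 people (protocol validation section). It is not stated to be the design SD.

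**Scale of the trial**
- Completers per arm: 29 × 0.70 = 20.3, so 20.
- Alpha, power and SD are not stated. With two-sided 5%, 80% power and SD 7.3 kg, n = 2 × (1.960 + 0.842)² × 7.3² / 6.5² = 19.8, so 20 per arm. Then 20 / 0.70 = 28.6, so 29. The planned 58 is thus reachable with an SD near 7.3 kg, and both SDs are carried forward.
- Standard error of the difference, SD × √(2/20): 2.66 kg with SD 8.4, and 2.31 kg with SD 7.3.

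**Shift in the treatment contrast**

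With a common mean offset b and home-weight shares p₁ and p₀, shift = b × (p₁ − p₀).

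| Assumed offset | Gap 0 points | Gap 20 points | Gap 30 points |
|---|---|---|---|
| 1 kg | 0 | 0.2 kg | 0.3 kg |
| 2 kg | 0 | 0.4 kg | 0.6 kg |

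- Relative to 6.5 kg: 0.2/6.5 = 3% to 0.6/6.5 = 9%.
- Relative to the standard error, the largest value is 0.6/2.66 = 0.23 or 0.6/2.31 = 0.26.
- At a more extreme 3 kg offset and a 30-point gap: 3 × 0.30 = 0.9 kg, or 14% of 6.5 kg and about a third of a standard error (0.9/2.66 = 0.34).

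**Added variance**

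If a share q of readings carries extra random error with SD e, the SD becomes √(8.4² + q × e²).
- q = 0.2, e = 1.5 kg: √(70.56 + 0.45) = 8.43 kg.
- q = 0.3, e = 2.5 kg: √(70.56 + 1.88) = 8.51 kg.
- At 20 per arm, even q = 0.5 with e = 3 kg lowers power (normal approximation) only from 68.7% to 66.0% with SD 8.4, and from 80.4% to 77.2% with SD 7.3.

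**Effect on the imputation trigger**

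Illustration: 30% of 58 is 17.4, say 17 participants without a clinic weight. If 9 of them gave home weights, 8/58 = 13.8% would count as missing, below the upper trigger of 15%. If 12 did, 5/58 = 8.6% would, below the lower trigger of 10%. Many who drop out will not report by telephone, so this shows the mechanism and is not a forecast.

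**Which time points are covered**

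The 2-year point falls after cessation and is plainly within the telephone clause. The 6-month point is less clear: the final treatment month is the taper, and the clause names the maintenance phase and the period after cessation, but not the taper. The same section later speaks of assessments at 6 and 24 months together, which suggests that both are meant.

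**The case against.** The strongest reply is that this is operational detail. A procedure manual exists and is said to standardise measurement, a journal article need not describe scale checks, and a source flag belongs in a case report form. The article also never says outright that home weights enter the primary analysis. Further, a telephone weight replaces no weight at all. In a 58-person trial expecting 30% attrition, losing those values could do more harm than an offset of a few tenths of a kilogram in the contrast. Finally, the route applies most clearly at 2 years, and the sample size section calls the 2-year analyses exploratory.

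Much of this stands. The fallback is worth keeping, the size is modest, and the manual may contain rules that cannot be seen here. What does not fall away is that the article itself introduces a second measurement route for the primary variable and describes the analysis as one of available data, with sensitivity analyses aimed only at missingness. The natural reading is that home weights are used like clinic weights. Although called exploratory in one section, the 2-year change is listed under the primary outcome in two others.

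A reader might go further and infer that mixed scales bias the primary result materially, or that the 6-month comparison is certainly affected. The documents support neither. Bias needs unequal use or unequal offset between arms, for which they give no evidence, and the telephone clause does not name the taper month.

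**Conclusion.** The point holds in a limited form. Unmarked and unpaired home weights can enter the change from a clinic baseline, clearly at 2 years and possibly at 6 months, and nothing planned would reveal an offset.

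The probable effect on the treatment contrast is 0.2 to 0.6 kg, at most about a quarter of a standard error. This rests on an assumed 1–2 kg offset and an assumed 20–30 point gap between arms. With equal use and equal offset it is zero. Loss of precision is negligible. This does not threaten the validity of the trial and is no reason to discard telephone weights. It is worth correcting because the repair is cheap and a baseline home reading cannot be obtained afterwards.

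**What to change.** Keep the telephone fallback, and add the following before enrolment:

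1. Record the source of every weight (clinic, or home by telephone).
2. Obtain a home-scale reading paired with the baseline clinic weight, repeated at a later clinic visit where possible. Compare a home follow-up weight with the home baseline, or correct it for the measured offset. This removes a stable scale difference. It does not fully remove misreporting or a change of scale.
3. Prespecify a sensitivity analysis using clinic-measured weights only, with home weights set to missing and handled by the planned multiple imputation, whether or not the 10–15% threshold is reached. Report it beside the primary analysis, not in its place.
4. State whether the telephone route applies at 6 months, and amend the data collection section so that it allows for that route.

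The cost is one data field and one or two home readings per participant. The sensitivity analysis will have fewer observed weights, so it will be less precise and will rely more on the imputation model, which is why it should not replace the primary analysis.

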### Reproducibility of study procedures

A comprehensive procedure manual has been created to standardise all aspects of the study, including patient recruitment, measurement assessment, data entry, management, analysis, and security. All study staff will receive training tailored to their specific roles. The manual includes detailed monitoring plans designed to safeguard patient welfare and ensure data integrity.

### Protocol validation

Poulton et al., treated 14 people with obesity with DEX for 6 months [5]. There was a mean weight loss of 10.6 ± 8.4 kg, (P < 0.001), with 7 participants (50%) losing >10% of their total body weight. Six months post DEX treatment, weight regain reduced the mean weight loss to 7.0 ± 10.6 kg (p = 0.035). However, 3 participants still recorded a weight reduction of >10% and 4–5 participants recorded a weight reduction between 5–10% of their baseline body weight. Other important clinical outcomes identified a reduction in the severity of obstructive sleep apnoea in one participant, a decrease in the amount of insulin required for diabetes control in another and a reduction in the number of antihypertensive medications in a third participant.

## Limitations

None.

## Related research article

None.

## Data Availability

No data was used for the research described in the article.
